#### Power and Sample Size Calculations

The primary outcome of the study is the total minutes of MVPA per week. MVPA is measured as “very active” and “fairly active” on Fitbit. The secondary outcome of the study is the patient’s self-report quality of life, measured by the 12-Item Short Form Survey [39]. We hypothesize the effect size of the iCanFit 2.0 to be 0.25, based on a prior Fitbit intervention trial [43]. Following the procedure developed by Cohen, the calculation of sample size is carried out in three steps by assuming a .05 significance level to achieve the power of 0.8 [44]. First, we assume that two independent samples can be obtained for the same size *n*_1_ each. Then the total sample size is *n*=2 x *n*_1_. In this ideal scenario, the total sample size *n*=398 is required to detect the effect size *d*=0.25 between the two population means. Second, because the randomization occurs at the clinic level, we need to consider the clustering effect. Previous similar research suggests a small clustering effect due to multiple patients per physician, but virtually no clustering effect between patients with different physicians in the same clinic [45]. We assume that if the intraclass correlation coefficient (ICC) per patient is equal to .05, and that ICC per physician is equal to 0, then equation 1 holds:

ICC=(1 + ICC_patient) x (1 + ICC_physican) – 1 = .05 (1)

Thus, the design effect is as follows in equation 2:

D=1 + (m - 1) x ICC (2)

where m is the average number of patients per physician in our effective sample. If we restrict m to be no more than 6, then D=1 + 5 x .05 = 1.25. We would need a sample size of 498 (ie, 398 x 1.25) after factoring in cluster effects. Third, based on our prior study of RCT primary care settings [36], we assume the attrition rate to be 0.2 after 12 months, thus the required sample size at baseline is 622 in total (ie, 498/[1-0.2]), or 52 patients per clinic on average. We will recruit no fewer than 30 and no more than 70 patients from each participating clinic.

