#### Data Analysis Plan

Our analysis has been planned to correspond to the study’s main aim. We will begin with exploratory data analyses. Demographic and baseline characteristics for the participants will be summarized using descriptive statistics overall and by intervention and control groups to assess baseline comparability. Prior to analyses, we will check continuous outcome distributions and apply normalizing transformation where needed.

Our main goal is to test the hypothesis that patients in the intervention group will have more MVPA per week than the control group. To test this hypothesis, we will compare major outcomes between the intervention and control groups. We will implement multi-level regression models (eg, hierarchical linear models and mixed-effect models). Multi-level regression models are needed to account for an ICC that results from clinic-level observations [45]. Patients’ observations over time are nested within PCPs, and PCPs are nested within clinics.

Equation 3 presents an example of a multi-level regression model for a continuous outcome Y_ijt_, on clinic *i*, PCP *j*, and time point *t*. Our analyses will also include background characteristics that are not included in equation 3 for the sake of brevity. Two predictors, time (TIME) and intervention group (INTV), are classified as 1=iCanFit and 0=control. The multi-level regression model is given as follows:

Y
_ijt_ = α
_0_ + INTV
_i_ × α
_1_ + TIME
_ijt_ × α
_2_ + INTV
_i_ X TIME
_ijt_ × α
_3_ + ζ
_ij_ + ε
_ijt_ (3)

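### The stated 80% power holds only if the clinic-level ICC is exactly zero: clinics are randomised, but the design effect of 1.25 counts at most 6 patients per physician

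*Protocol article*

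**What the plan says.** In the protocol article, Power and Sample Size Calculations brings in clustering with the reason that "because the randomization occurs at the clinic level, we need to consider the clustering effect". It then relies on a cited source for a small correlation among patients of one physician and "virtually no clustering effect between patients with different physicians in the same clinic". Equation 1 combines an ICC of .05 (same physician) with an ICC of 0 (different physicians, same clinic) into a single ICC of .05. Equation 2 is D = 1 + (m - 1) x ICC, "where m is the average number of patients per physician in our effective sample". With m limited to 6, D = 1.25, which takes 398 to 498 and, after 20% attrition, to 622 at baseline, or 52 per clinic.

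The only recruitment limit given is per clinic: "We will recruit no fewer than 30 and no more than 70 patients from each participating clinic".

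The Data Analysis Plan, citing the same source, says "Multi-level regression models are needed to account for an ICC that results from clinic-level observations". The example model in equation 3 has a random intercept for each physician within a clinic and no clinic term.

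**The concern.** In a cluster randomised trial the variance of the treatment comparison depends on how alike patients are within the randomised unit, here a clinic. Using patients per physician as the cluster size is valid only if patients of different physicians in one clinic are uncorrelated. That is the most favourable non-negative value the clinic ICC can take, and the plan shows no other. With about 41.5 retained patients per clinic, even a very small clinic ICC is multiplied by a large number. The two sections also describe clinic-level correlation differently while citing one source. At stake is the power stated for the primary outcome, minutes of moderate-to-vigorous activity per week. With only 12 clinics, a shortfall found later may not be recoverable by enrolling more patients at the same sites.

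**Working it through.** **Inputs from the protocol article.** Effect size: "We hypothesize the effect size of the iCanFit 2.0 to be 0.25". Error rates: "assuming a .05 significance level to achieve the power of 0.8", with sidedness not stated. Twelve clinics in six pairs; same-physician ICC .05; m = 6; 498 retained; 20% attrition. The article gives no non-zero clinic ICC, so the values below are assumptions.

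**1. The plan's own figures.** A one-sided t-test at .05 with 80% power and d = 0.25 needs 198.5 per arm, so 199 per arm and 398 in total. A two-sided test needs 504 (normal approximation), so 398 is a one-sided figure. D = 1 + 5 x .05 = 1.25; 398 x 1.25 = 497.5, rounded to 498; 498/0.8 = 622.5 (stated as 622); 622/12 = 51.8 per clinic. The chain reproduces. I stay on the one-sided basis below so that the separate question of sidedness does not enter.

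**2. Design effect with a clinic ICC.** Retained patients per clinic: M = 498/12 = 41.5. With physicians nested in clinics,

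D = 1 + (m - 1) x rho_physician + (M - m) x rho_clinic = 1.25 + 35.5 x rho_clinic,

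where rho_physician = .05 is the correlation between two patients of the same physician and rho_clinic that between patients of different physicians in one clinic. At rho_clinic = 0 this returns the plan's 1.25.

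**3. Power.** SE = sqrt(4D/498) in standard-deviation units and ncp = 0.25/SE. Normal-theory power is Phi(ncp - 1.645). The last column uses the non-central t with 12 - 2 = 10 between-clinic degrees of freedom.

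| rho_clinic (assumed) | D | ncp | Power, normal | Power, t on 10 df |
|---|---|---|---|---|
| 0 | 1.25 | 2.495 | 80% | 75% |
| .005 | 1.43 | 2.335 | 76% | 70% |
| .01 | 1.61 | 2.202 | 71% | 66% |
| .02 | 1.96 | 1.992 | 64% | 58% |
| .05 | 3.03 | 1.604 | 48% | 44% |

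**4. What equations 1 and 2 would do with a clinic ICC.** Put .01 into equation 1: 1.05 x 1.01 - 1 = .0605. Equation 2 then gives D = 1 + 5 x .0605 = 1.30. The nested form gives 1.25 + 35.5 x .01 = 1.61. The plan's formulas multiply the clinic ICC by about m - 1 = 5, so a non-zero value cannot simply be inserted.

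**5. Can more patients per clinic restore 80%?** Set 12M/D = 398, with m kept at 6. At rho_clinic = .01, M = 398 x 1.19/(12 - 3.98) = 59 retained. At .02, M = 398 x 1.13/(12 - 7.96) = 111. The recruitment ceiling of 70 per clinic leaves 70 x 0.8 = 56 retained. At .05, 398 x .05 = 19.9 exceeds 12, so no M is enough with 12 clinics; one-sided normal-theory power then has a ceiling of about 61%.

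**6. Does the recruitment rule deliver m = 6?** At six retained patients per physician, 498/6 = 83 physicians are needed, about 7 per clinic. The article states neither a number of physicians nor a per-physician limit on recruitment. If m were 10, D would be 1 + 9 x .05 = 1.45 even at rho_clinic = 0.

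**The case against.** The strongest reply is that nothing has been miscalculated. The zero is a stated assumption with a citation, the chain 398, 498, 622 follows from it, and the three-level formula gives the same 1.25 at that value. The cited source is not at hand, so the zero cannot be called false. Equation 3, with a physician intercept only, agrees with it. If physicians really are the only clusters, the 83 physicians supply about 81 degrees of freedom and one-sided power is about 80%, so the 75% in the first row depends on testing at clinic level. All of this stands, and the concern is therefore about an untested boundary assumption.

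It is also fair that the planned test is of the group-by-time term. A clinic effect that is constant over time would largely cancel there, and only clinic-by-time variation would inflate the variance. Pairing and covariates may help as well. The sample-size section, however, uses none of these; it is built on a comparison of two means. Clinic sizes varying from 30 to 70 would work the other way.

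Three stronger readings are tempting but not supported:

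- That the Data Analysis Plan refutes the zero. It contains one phrase about a clinic-level ICC, and the model that follows has no clinic term. The wording is in tension with the zero but does not disprove it.
- That coaching adds clinic-level correlation. Sessions take place in clinics, but the article does not say how coaches are allocated to clinics.
- That the true design effect is 3.03. That figure applies the plan's same-physician ICC to whole clinics, which the plan does not do; it is only the upper end of an assumed range.

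**Conclusion.** The point stands as one of conditional power. D = 1.25 is likely understated, and 80% is the best case under non-negative clinic correlation, not a central estimate. Near-absence of clinic clustering is not the same as zero when it is multiplied by 35.5. A clinic ICC of .005 already lowers normal-theory power to 76%, .01 to 71% and .02 to 64%. If the test uses between-clinic degrees of freedom, power is 75% even at an ICC of 0.

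These figures rest on a one-sided .05 test, 498 retained, m = 6, equal clinic sizes, an end-point comparison without adjustment or credit for pairing, and clinic ICCs that are assumed. The direction for such a comparison is not in doubt; the size depends on a quantity the article does not give. The correction matters because the sample size for the primary outcome relies on this figure and, according to the article's Results section, the trial was still seeking funding, so it can be made before enrolment.

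**What to change.** Rewrite the clustering step of Power and Sample Size Calculations:

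1. Replace equations 1 and 2 with D = 1 + (m - 1) x rho_physician + (M - m) x rho_clinic, where M is the number of analysed patients per clinic.
2. Use t critical values with between-clinic degrees of freedom (10, or 5 if the analysis is by pair).
3. Give power over a range of clinic ICCs, for example 0 to .05, labelled as assumed, and state that 80% is the value at zero. If credit is taken for pairing, covariates or the group-by-time contrast, state the assumptions behind it.
4. Either add the limit of 6 per physician to the recruitment rule or use the m that 30 to 70 patients per clinic will produce.
5. Bring the sentence on clinic-level ICC in the Data Analysis Plan into line with the assumption used for sample size.

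The cost is one rewritten paragraph and a less favourable stated power. No additional clinics or patients are requested.

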#### Data Analysis Plan

Our analysis has been planned to correspond to the study’s main aim. We will begin with exploratory data analyses. Demographic and baseline characteristics for the participants will be summarized using descriptive statistics overall and by intervention and control groups to assess baseline comparability. Prior to analyses, we will check continuous outcome distributions and apply normalizing transformation where needed.

Our main goal is to test the hypothesis that patients in the intervention group will have more MVPA per week than the control group. To test this hypothesis, we will compare major outcomes between the intervention and control groups. We will implement multi-level regression models (eg, hierarchical linear models and mixed-effect models). Multi-level regression models are needed to account for an ICC that results from clinic-level observations [45]. Patients’ observations over time are nested within PCPs, and PCPs are nested within clinics.

Equation 3 presents an example of a multi-level regression model for a continuous outcome Y_ijt_, on clinic *i*, PCP *j*, and time point *t*. Our analyses will also include background characteristics that are not included in equation 3 for the sake of brevity. Two predictors, time (TIME) and intervention group (INTV), are classified as 1=iCanFit and 0=control. The multi-level regression model is given as follows:

Y
_ijt_ = α
_0_ + INTV
_i_ × α
_1_ + TIME
_ijt_ × α
_2_ + INTV
_i_ X TIME
_ijt_ × α
_3_ + ζ
_ij_ + ε
_ijt_ (3)

where α_0_, α_1_, α_2_, and α_3_ are the fixed effects, ζ_ij_ is a random effect (ie, random intercept) for each PCP in each clinic, and ε_ijt_ is the residual error for repeated observations over time. The random effect is assumed to be normally distributed with mean zero. The residual error is assumed to be multivariate normally distributed across repeated observations, with mean zero and a covariance matrix that models the autocorrelation among repeated observations [46]. We will examine model fit statistics to choose an appropriate covariance structure. Hypothesis testing will be carried out to test for intervention effects on the outcome of interest over time. Referring to equation 3, this is equivalent to testing the hypothesis H_0_: α_3_ = 0. If higher outcome values are desirable, then a positive significant α_3_ parameter indicates a positive intervention effect (ie, we reject H_0_: α_3_ = 0). We will use the SAS version 9.0 (SAS Institute Inc) PROC MIXED procedure and PROC GLIMMIX procedure to fit multi-level models to continuous and binary data, respectively.

We will also apply structural equation modeling (SEM) to examine the extent to which the intervention takes effect at individual, interpersonal, health care, and community levels as shown in Figure 1. Models will be constructed to measure direct and indirect effects. We will also analyze whether increased MVPA is a mediator for improved clinical outcomes. Latent variables are similar to random effects, accounting for nested observations. We will use Mplus version 3.1 (Muthén & Muthén) to fit SEM for continuous and binary data [47,48].

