### Intervention Trial

#### Overview

The intervention trial compares the effectiveness of the iCanFit 2.0 intervention program with a comparator program among overweight older adults in a primary care setting. To achieve this goal, we will conduct a cluster RCT in 12 family medicine clinics (six pairs) in Central Texas, USA. In each pair of comparable clinics, one will be randomized to the intervention group and one to the control group (see Figure 2).

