#### iCanFit 2.0 Intervention Protocol

As illustrated in Figure 3, the iCanFit 2.0 intervention protocol includes four steps. First, after the eligible participants complete the informed consent forms, they will complete an HBA on an iPad (see Multimedia Appendix 1 for sample screenshots), which takes about 15 minutes. Right after completion, patients will receive a printed copy of the HBA summary report with colorful charts of their current level of physical activity compared to the recommended physical activity levels (see sample summary reports in Multimedia Appendix 1). Meanwhile, the same report will be printed out in the office of the PCP with whom the patient has an appointment. Second, the patient brings the HBA report into his/her appointment with the PCP and the report serves as a natural conversation starter to facilitate patient-provider communication and joint goal setting. Third, right after the patient’s appointment with the PCP in the primary care clinic, a health coach will meet with the patient, further explain the HBA report, and ensure the patient has set a long-term physical activity goal, if the patient has not set one with the PCP. The health coach will give the patient a Fitbit Flex 2 (Fitbit Inc) (see Multimedia Appendix 2 and section below about the device) and demonstrate how to use the device. The health coach will also help the patient to create an account on the iCanFit online community. The health coach will advise on how to set short-term (eg, weekly) goals, track and sync data, share progress with family and friends via Facebook, and obtain personalized feedback on the iCanFit online community. The counseling session will last 30 minutes; a photo-illustrative brochure with instructions on how to use the Fitbit as well as account information and reminders will be given to the patient. Fourth, the health coach will constantly monitor patients’ use of the Fitbit and iCanFit online community. Patients will receive incentives (eg, online badges, virtual coins, and honor levels) for meeting physical activity goals and updating their progress. Any questions posted on the iCanFit online community will be answered by the health coach within 12 hours. If a patient is “idle” for 2 weeks, the health coach will call the patient to offer help and address the patient’s barriers. Patients will also receive a brochure of safety tips (see Multimedia Appendix 3), which details possible adverse events during exercise and how to take action depending on the situation. For adverse events that need immediate medical attention, patients are advised to go to the nearest emergency room. For nonurgent matters, they can contact the health coach, who can assist with scheduling a clinic appointment with the patient’s PCP.

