#### Comparator

The patients in the control group will receive usual care enhanced with a Fitbit Flex 2, as shown in Multimedia Appendix 2. The Fitbit Flex 2 was released in 2016, costs US $75, and weighs a quarter of an ounce. It is compatible with iPhones and Android phones, only needs to charge once a week, syncs automatically with mobile phones within 20 feet, and easily syncs to a computer with a USB port. It tracks steps taken, stairs climbed, calories burned, distance travelled, and sleep time. Figure 4 illustrates the process of the comparator protocol. After eligible patients provide informed consent, they will first complete an HBA on an iPad while waiting for their appointment. Unlike patients in the intervention group, patients in the control group will not receive any reports from their HBA; after their appointment with the PCP, they will receive a Fitbit Flex 2 and a brochure explaining how to use the Fitbit and the benefits of regular physical activity. Patients in the control group will not be given any information about the iCanFit online community; neither will they receive counseling or monitoring from health coaches. Similar to the intervention group, control group patients will receive the safety tips of exercise brochure.

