### Outcome Evaluation

#### Outcome Measures and Sources of Data

The evaluation of the iCanFit, physical activity-promotion program will be based on three datasets:

HBA surveys collected using the iPad at baseline and two follow-up surveys. As shown in Table 1, the survey includes demographic information, technology use and eHealth literacy [37], current level of physical activity [38], quality of life [39], patient-provider communication [40], perceived support from the health care team [41], and perceived social support for physical activity from the community [42]. All of these measures are based on validated scales with good validity and reliability. The first follow-up is a phone survey 3 months after baseline and the second follow-up is a clinic visit 6 months after baseline. This arrangement is based on the consideration that all overweight older adults are asked to visit their PCP at least every 6 months [27].Fitbit data. Two types of Fitbit data will be collected for evaluation: physical activity data recorded on Fitbit and patient interactions with the health coaches and peers in the iCanFit online community.Clinic data. We will collect patients’ weight and adverse events related to participating in the study from the EHRs at the clinic visits at baseline and at the 6-month follow-up.

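### Coaches treat the intervention arm only, yet neither D = 1.25 nor equation 3 allows for clustering by coach or clinic; if coaches differ, power is overstated and the α₃ test is too liberal

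*Protocol article*

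**What the plan says.** All references are to the protocol article.

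- **Who delivers the intervention (iCanFit 2.0 Intervention Protocol).** After the physician appointment, "a health coach will meet with the patient, further explain the HBA report, and ensure the patient has set a long-term physical activity goal" where none was set with the physician. The coach also runs the 30-minute session, monitors device and community use, answers posted questions within 12 hours and telephones patients who have been idle for 2 weeks.
- **Controls (Comparator).** They get the device and brochures; "neither will they receive counseling or monitoring from health coaches".
- **Randomisation (Intervention Trial, Overview).** There are six pairs of clinics. In each pair, "one will be randomized to the intervention group and one to the control group".
- **Sizing (Power and Sample Size Calculations).** "We hypothesize the effect size of the iCanFit 2.0 to be 0.25", and the calculation proceeds "by assuming a .05 significance level to achieve the power of 0.8". The design effect uses m = 6 patients per physician and an ICC of .05, giving D = 1.25. Clustering between patients of different physicians in one clinic is taken as practically nil, on the strength of earlier research.
- **Model (Data Analysis Plan).** The stated structure is that "observations over time are nested within PCPs, and PCPs are nested within clinics". Equation 3 has fixed effects for arm, time and their interaction, one random intercept ζ for the physician within the clinic, and a residual. The test is of α₃, the arm-by-time interaction. There is no clinic term and no coach term.

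**The concern.** The coach is a treatment provider who exists in one arm only. If some coaches are more effective than others, patients of the same coach will have correlated outcomes after baseline, whoever their physician is. The assumption that patients of different physicians are nearly independent was taken from earlier research. It cannot simply be carried over to an arm in which the trial itself adds a provider who may work across those physicians.

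Two things are at stake. The sizing would understate the variance of the intervention-arm mean, so that power falls short of 80%. The analysis would also give α₃ too small a standard error, so that chance differences between coaches could be read as an effect of iCanFit 2.0. Equation 3 is exposed on the second count because a random intercept that is constant over time drops out of a change over time. It therefore cannot absorb coach effects that arise only after treatment starts.

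**Working it through.** **1. Reproduce the plan's chain.** With d = 0.25, α = .05 and power 0.8, a t-test calculation gives a total of 398 one-sided and 506 two-sided. The plan's 398 is therefore the one-sided figure. The article does not state the sidedness, though its hypothesis is directional: "patients in the intervention group will have more MVPA per week than the control group". Then D = 1 + 5 × .05 = 1.25; 398 × 1.25 = 497.5, rounded to 498; 498/0.8 = 622.5 (stated as 622). Retained patients: 498/2 = 249 per arm and 498/12 = 41.5 per clinic.

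Check: SE = √(1.25/249 + 1.25/249) = 0.1002; 0.25/0.1002 − 1.645 = 0.85; power 80%.

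**2. Are coaches likely to be shared across physicians?** At no more than 6 retained patients per physician, 249/6 = 41.5, so the intervention arm needs about 42 physicians. Unless there are about as many coaches as physicians, a coach serves patients of several physicians. This is an inference, because the number of coaches is not given.

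**3. Power with a coach component.** Assumptions: one coach per intervention clinic (41.5 retained patients each), coach ICC ρ in the intervention arm only, and physician clustering as the plan has it.

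D_int = 1.25 + (41.5 − 1) × ρ; D_control = 1.25; SE = √[(D_int + 1.25)/249]; power = Φ(0.25/SE − 1.645).

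| ρ | D_int | mean D | SE | power, one-sided | baseline N for 80%, caseload fixed |
|---|---|---|---|---|---|
| 0 | 1.25 | 1.25 | 0.100 | 80% | 622–623 |
| .01 | 1.66 | 1.45 | 0.108 | 75% | 724 |
| .02 | 2.06 | 1.66 | 0.115 | 70% | 824 |
| .05 | 3.28 | 2.26 | 0.135 | 58% | 1127 |

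The last column is 398 × mean D / 0.8, rounded up at each step.

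Range over caseload: 24 coaches (10.4 patients each) at ρ = .01 gives D_int = 1.25 + 9.375 × .01 = 1.34 and 79% power. Three coaches (83 each) at ρ = .05 gives D_int = 1.25 + 82 × .05 = 5.35 and 46% power.

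**4. Type I error.** Simulated trials with no average treatment effect: 6 + 6 clinics, 7 physicians per clinic, 6 patients per physician, physician ICC .05, coach effect in the intervention arm only, two-sided 5% tests.

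| Test | ρ = .01 | ρ = .02 | ρ = .05 |
|---|---|---|---|
| t test on physician means, one coach per clinic | 6.6% | 8.2% | 13% |
| t test on clinic means, one coach per clinic | 5.1% | 5.1% | 5.5% |
| t test on clinic means, each coach covering two clinics | 6.7% | 8.5% | 12% |

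These are approximate; repeat runs differ by a few tenths of a point, at most about half a point.

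The α₃ test itself was also simulated, as a comparison of mean change with a coach effect arising after baseline, six coaches and an assumed within-patient correlation of 0.6. The physician intercept cancels. Type I error was 8.0%, 10.8% and 19.3% for the same three values of ρ, and 5.0% at ρ = 0. With twelve coaches it was 6.3%, 8.3% and 12.3%.

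**The case against.** **With one coach per clinic, this is largely the missing clinic term.** Coach and clinic are then the same unit in the intervention arm, and the second row of the type I table shows that a clinic-level test restores about 5%. This stands, and the fix relies on it. It does not rescue the plan, because equation 3 has no clinic term although clinics are named as a level. Nor does it restore power: the table in step 3 applies whichever valid test is used.

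**The size is assumed throughout.** This also stands. Training, supervised practice and random session checks by a nurse (Program Fidelity) are meant to keep coaches alike and may hold the coach ICC down. If the programme has no effect on anyone, coaches cannot differ in effect; inflation needs a null average with coaches varying around it.

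**Equation 3 is offered as an example in a condensed article.** This is fair as to detail. But the article does fix the design effect, the clustering levels and the parameter tested, and none of them allows for the coach.

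**Stronger readings that the documents do not support.** A reader might infer that intervention clinics are not independent because coaches work across them. The text does not say so. Coaches are notified at check-in and meet the patient straight after the appointment, which suggests on-site staff; coverage of two clinics is merely not excluded. A reader might also count the data on "patient interactions with the health coaches and peers in the iCanFit online community" as evidence of further clustering that the model should carry. Dependence shared by the whole intervention arm cannot be separated from the treatment effect, so no random effect can estimate it, and it is not part of this point.

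**Conclusion.** The point holds conditionally. Given a positive coach ICC and coaches shared across physicians, D = 1.25 is too small for the intervention arm, the stated 80% power is too high, and the α₃ test in equation 3 is anti-conservative. With one coach per clinic and a coach ICC of .01 to .05, power is about 75% to 58% on the plan's implicit one-sided basis. The effect ranges from negligible (24 coaches, ICC .01) to severe (3 coaches, ICC .05: 46% power). It would be wrong to say that type I error does exceed 5% in this trial, since that depends on coach variation that the documents do not quantify. Respecting the randomised clinic cures the type I error if coaches stay within clinics. It does not cure the power shortfall, and it fails if a coach covers more than one intervention clinic.

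**What to change.** 1. Record the coach identifier for every intervention patient.
2. Assign each coach to one intervention clinic only, so that coach effects stay inside a randomised unit. This has to be settled before the start.
3. Add to equation 3 a clinic effect and, where a clinic has more than one coach, a coach effect confined to the intervention arm. Each must act on the change over time that α₃ tests, not only on the intercept, and be used with small-sample degrees of freedom.
4. In Power and Sample Size Calculations, state the planned number of coaches and their caseload, and restate the design effect and power over a range of caseloads and coach ICCs.

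The cost is one logged variable, an assignment rule, one or two model terms and a revised calculation. According to Results, the trial is still seeking funding, so all of this can be done now. The downside is wider intervals and a less favourable stated power, or a larger sample if 80% is to be kept. The assignment rule may also reduce flexibility in staffing.
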